## Abstract

**Background:**

Depression is often a chronic relapsing condition, with relapse rates of 50-80% in those who have been depressed before. This is particularly problematic for those who become suicidal when depressed since habitual recurrence of suicidal thoughts increases likelihood of further acute suicidal episodes. Therefore the question how to prevent relapse is of particular urgency in this group.

**Methods/Design:**

This trial compares Mindfulness-Based Cognitive Therapy (MBCT), a novel form of treatment combining mindfulness meditation and cognitive therapy for depression, with both Cognitive Psycho-Education (CPE), an equally plausible cognitive treatment but without meditation, and treatment as usual (TAU). It will test whether MBCT reduces the risk of relapse in recurrently depressed patients and the incidence of suicidal symptoms in those with a history of suicidality who do relapse. It recruits participants, screens them by telephone for main inclusion and exclusion criteria and, if they are eligible, invites them to a pre-treatment session to assess eligibility in more detail. This trial allocates eligible participants at random between MBCT and TAU, CPE and TAU, and TAU alone in a ratio of 2:2:1, stratified by presence of suicidal ideation or behaviour and current anti-depressant use. We aim to recruit sufficient participants to allow for retention of 300 following attrition. We deliver both active treatments in groups meeting for two hours every week for eight weeks. We shall estimate effects on rates of relapse and suicidal symptoms over 12 months following treatment and assess clinical status immediately after treatment, and three, six, nine and twelve months thereafter.

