## Methods/Design

This is a multi-centre, randomised controlled trial. We randomise participants between Mindfulness-Based Cognitive Therapy (MBCT) in addition to Treatment As Usual (TAU), Cognitive Psycho-Education (CPE) in addition to TAU, and TAU alone. In doing so, we stratify participants by (a) research centre (Oxford or Bangor) (b) cohort (c) history of suicidality (none, ideation or suicidal attempt) and (d) whether or not they were taking antidepressants in the 7 days before their first assessment. We originally proposed to stratify by centre, cohort, suicidal behaviour (ideation versus attempt), number of previous episodes of depression (3 or 4 versus 5 or more), and brooding (high versus low scores on a subscale of the Ruminative Response Style questionnaire). However we later changed these, with ethical approval, to reflect the inclusion of participants taking antidepressants or without suicidal ideation. We undertake randomisation by e-mail to the remote randomisation centre at the North Wales Organisation for Randomised Trials in Health (NWORTH) at Bangor University. The randomisation algorithm uses dynamic allocation to protect against subversion while ensuring that each arm of the trial is comparable with respect to the stratification variables. For validation the randomisation e-mail also includes additional information including the participant's date of birth, gender and date of assessment.

We monitor treatment effects over a period of one year. Assessments by trained assessors who are blind to treatment allocation (and whose blindness is checked within each assessment session) take place directly before and after the start of the treatment (T0 and T1), and at three (T2), six (T3), nine (T4) and twelve months (T5) after T1 (see Figure 1 for details of participant flow through the trial). We also offer treatment 'reunions' to participants in both MBCT and CPE at both 6-8 weeks and 6 months after treatment.

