### Post-Treatment Assessment and Follow-Ups

Once treatment is finished, we invite all participants to a post-treatment assessment. Over the following 12 months we invite them to attend research assessments at three, six, nine and twelve months after treatment. We also invite those allocated to treatment with MBCT or CPE to attend two treatment sessions, one 6-8 weeks, the other six months after treatment. At post-treatment assessment (T1), we use the SCID mood disorder module to assess current diagnostic status and any changes in that status over the treatment phase. We ask participants to repeat the cognitive tasks and questionnaires they completed during the pre-treatment assessments with the exception of the Childhood Trauma Questionnaire (CTQ), the worst ever BSS, the crisis card, and questions about sociodemographic status. The follow up assessments at three (T2), six (T3) and nine months (T4) consist of a SCID mood disorder module, the Hamilton Rating Scale for Depression and, when there has been suicidal behaviour or self harm, the SASII assessment, focusing on the time since the last assessment. We also ask them to complete questionnaires assessing current symptoms and history of treatment since last assessment (BSS current, Suicide Cognitions Questionnaire, MINI Suicidality Tracking, BDI-II, BHS, Life Events Questionnaire, CORE, Euro-QOL, PHQ9, GAD7). During the final follow-up assessment (T5), we ask participants to complete the same measures as at the T1 assessment. Additional File 1 includes a table summarizing all these baseline and follow-up assessments.

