### Analysis

We shall analyse all data by intention to treat. We shall use Cox regression, a form of survival analysis that takes account of covariates, to analyse relapse and recurrence. We shall analyse most other measured variables by mixed-model analysis of variance (ANOVA). We shall use baseline values of the dependent variable as a covariate in all analyses; we shall use other baseline measures or demographic characteristics as covariates when they contribute significantly to the analysis. We shall use multi-level modeling to take account of the clustering of participants within classes within centres. To minimise testing, we shall combine measured outcomes at different time points using the 'area under (the resulting) curve'. We shall use cognitive measures to explore the extent to which they mediate relapse and recurrence during treatment and follow up. Similarly we shall use data at each time-point on the Beck Scale for Suicide Ideation to explore the extent to which the cognitive measures mediate the occurrence of suicidality over the follow-up period, again analysing 'area under the curve'. Additionally we shall examine recurrence of suicidality specifically for those participants who relapse to Major Depression (MDD) and had a history of suicidal ideation or behaviour at entry to the trial. We predict that, all else being equal, suicidal ideation will fall in those who have received treatment with MBCT. Further details of the data analysis plans are given in Appendix 1.

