## Appendix 1: Statistical Analysis Plan

The primary outcome measure will be the time to relapse or recurrence meeting DSM-IV criteria for a major depressive episode (American Psychiatric Association, 1994) on the Structured Clinical Interview for DSM-IV (SCID, Spitzer et al., 1992). Occurrence of relapse or recurrence will be assessed after treatment (T1), and at three (T2), six (T3), nine (T4) and twelve (T5) months thereafter by trained psychologists blind to participants' treatment condition. If the interview establishes that symptoms meeting diagnostic criteria for major depression have been present since the last assessment, we shall ask participants when this episode of depression started (and ended, if they are no longer symptomatic). 'Return to treatment' will also be treated as a relapse or recurrence if, in the judgment of a blind rater, the participant experienced exacerbation of their symptoms that would have met the criteria for Major Depression in the absence of immediate treatment.

The analysis will be by 'intention to treat' (ITT). The time (in weeks) of relapse or recurrence to Major Depression, as defined above, will be the dependent variable in survival analysis. The treatment group and stratification variables will be used as predictors.

For participants who are lost from the trial we shall use their available measures and then censor them at the time of their last observation. Since only a participant's first relapse or recurrence to Major Depression will contribute to the survival analysis, the subsequent loss of that participant will not affect the analysis.

Participants who miss one or more follow-up assessments, but are then assessed at a later time point will be asked whether they have experienced a relapse or recurrence according to SCID diagnostic criteria since the last assessment, including time periods which would have been covered in missed assessments. This will enable us to assess the time to relapse and thus to censoring.

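### The window for the primary relapse outcome is stated inconsistently and the survival clock has no stated origin, so relapses between randomisation and T1 could be counted or left out

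*Protocol article*

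**What the plan says.** Four places in the protocol article bear on the window for the primary outcome.

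- **Abstract, Methods/Design:** "We shall estimate effects on rates of relapse and suicidal symptoms over 12 months following treatment". The window opens at the end of treatment.
- **Methods/Design (main text):** "We monitor treatment effects over a period of one year". No start is given. The later visits are placed "at three (T2), six (T3), nine (T4) and twelve months (T5) after T1", so a year of follow-up counted that way also begins at T1.
- **Post-Treatment Assessment and Follow-Ups:** the SCID mood module is used at T1 "to assess current diagnostic status and any changes in that status over the treatment phase".
- **Appendix 1, Statistical Analysis Plan:** "Occurrence of relapse or recurrence will be assessed after treatment (T1), and at three (T2), six (T3), nine (T4) and twelve (T5) months thereafter". Participants with an episode since their last assessment are asked when it began.

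The analysis variable is then given as follows: "The time (in weeks) of relapse or recurrence to Major Depression, as defined above, will be the dependent variable in survival analysis". Appendix 1 declares intention to treat, uses only the first relapse, and censors at the last observation. It does not say from which date the weeks are counted. Outcome Measures says relapse is assessed at every follow-up assessment, without saying whether T1 is one of them.

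**The concern.** A relapse in, say, the fifth week of classes lies outside the Abstract's window but inside the period that Appendix 1 assesses. With no time zero, the text does not settle whether it is a primary event, or at what time it occurred.

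Randomisation comes after the second pre-treatment assessment and before the pre-class interviews and eight weekly classes. Randomisation and T1 are therefore at least about two months apart. If the clock starts at T1, a participant who relapsed earlier must be removed or has no valid event time. Those left are selected on an event that happened after randomisation and that treatment may affect. That is not an intention-to-treat comparison.

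The two readings give different estimands and different event counts. A choice left open could be made after the data are seen. The mediation analysis in Appendix 1 is also affected: it uses change from T0 to T1 to explain relapse, and a relapse before T1 precedes or overlaps that mediator.

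**Working it through.** **Inputs from the documents.** Sample Size gives 120 MBCT, 120 CPE and 60 TAU, a 5% significance level, and relapse of 39%, 57% (CPE in the power statement) and 70%. Stated power is 80% for MBCT v CPE and 99% for MBCT v TAU. The Interventions gives eight weekly classes. Methods/Design places T5 twelve months after T1.

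**Assumptions.** Two-sided test, constant hazards, no loss to follow-up, and 8 weeks from randomisation to T1. The documents give neither the interval from randomisation to the first class nor the period to which the planning rates apply.

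**1. The plan's own figures.** HR = ln(1 − p₁)/ln(1 − p₂); events = Σ n·p; Schoenfeld power = Φ(√(D·a(1 − a))·|ln HR| − 1.96), where D is the number of events and a the share in MBCT.

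- MBCT v CPE: HR = ln 0.61/ln 0.43 = 0.586; D = 120 × 0.39 + 120 × 0.57 = 115.2; power 81.9% (80.1% by Freedman's formula). Stated: 80%.
- MBCT v TAU: HR = ln 0.61/ln 0.30 = 0.411; D = 46.8 + 42 = 88.8; power 97.7% (99.1% by Freedman). Stated: 99%.

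The sample size reproduces. It is not in question here.

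**2. Relapses before T1, with the planning rates taken to span randomisation to T5 (8 + 52 = 60 weeks).** Fraction before T1 = 1 − (1 − p)^(8/60).

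| Arm | Fraction before T1 | Participants |
|---|---|---|
| MBCT | 1 − 0.61^0.1333 = 6.4% | 7.7 of 120 |
| CPE | 1 − 0.43^0.1333 = 10.6% | 12.8 of 120 |
| TAU | 1 − 0.30^0.1333 = 14.8% | 8.9 of 60 |

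**3. Effect of removing them.**

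- MBCT v CPE: 115.2 − 7.7 − 12.8 ≈ 95 events; power 81.9% → 74.0%.
- MBCT v TAU: 88.8 − 7.7 − 8.9 ≈ 72 events; power 97.7% → 93.9% (about 96% in a 4,000-replicate log-rank simulation).
- With 12 weeks to T1 instead of 8, MBCT v CPE has 87 events and 70.3% power.

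**4. Other assumptions, MBCT v CPE, 8 weeks to T1 (log-rank simulation).**

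| Assumption | Power from randomisation | Power from T1, early relapsers removed |
|---|---|---|
| Rates span randomisation to T5, same HR throughout | 82% | 74% |
| Rates apply to the 52 weeks after T1, same HR throughout | 85% | 77% |
| As the row above, but MBCT has no benefit until T1 | 66% | 76% |

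The origin moves power by about 8 to 10 points, and the direction depends on when the treatment starts to act.

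**The case against.** The strongest reply is that the operative text already points one way. Appendix 1 lists T1 among the assessments of the primary outcome, dates the onset of any episode since the previous assessment, defines the survival variable by reference to that text, and declares intention to treat. The Abstract sentence also goes on to mention an assessment immediately after treatment, and can be read as giving only the length of follow-up. No section orders a T1 start or the exclusion of early relapsers. All of this stands, and it means the harm is conditional. It does not supply a time zero or remove the different window in the Abstract.

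It can also be said that an article leaves such detail to a fuller plan. That carries less weight here. The appendix is titled as the statistical analysis plan and goes into censoring, missed visits and imputation, and the window wording is stated text that conflicts.

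Three stronger readings are tempting, but the documents do not support them.

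- A reader might cite the phrase "mediate relapse and recurrence during treatment and follow up" in the Analysis section as a definition of the primary window. It describes the exploratory mediation analysis.
- A reader might argue that TAU participants have no treatment start or end, so T1 is undefined for them. All participants complete weekly questionnaires through the eight-week treatment phase and all are invited to the post-treatment assessment, so TAU shares the timetable.
- A reader might infer that a T1 start necessarily lowers power. If MBCT acts only after T1, it raises power.

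**Conclusion.** The point holds as an inconsistency in the primary risk window together with a missing time origin. A reader might infer that the plan breaks intention to treat. It does not prescribe that; it leaves open a reading that would, while Appendix 1 leans the other way.

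The illustrated size is about 6%, 11% and 15% of MBCT, CPE and TAU participants relapsing before T1, with MBCT v CPE power going from about 82% to 74% if they are removed. These figures rest on a constant hazard, an 8-week interval, planning rates spanning randomisation to T5 and no loss to follow-up, none of which the documents fix. The power figures show sensitivity to the origin and do not predict a loss. The firmer reason to act is the unequal removal by arm: when relapse before T1 differs between arms, a comparison from T1 among those still well is no longer the randomised comparison.

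**What to change.** In Appendix 1, state that time to first relapse or recurrence is counted in weeks from randomisation in all three arms, up to T5; that a relapse during the treatment phase is a primary event at its dated onset; and that every randomised participant is at risk from time zero. Align the wording of the Abstract, the one-year statement in Methods/Design, and Outcome Measures, where it should be clear that T1 is included. If an effect from the end of treatment is also of interest, label a landmark analysis from T1 among those still relapse-free as supportive only.

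The cost is wording. Appendix 1 already collects episode onset dates, and allocation goes through a remote randomisation centre, so the date of randomisation should be on record. No visit, measure or sample size changes.

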**Discussion:**

This will be the first trial of MBCT to investigate whether MCBT is effective in preventing relapse to depression when compared with a control psychological treatment of equal plausibility; and to explore the use of MBCT for the most severe recurrent depression - that in people who become suicidal when depressed.

**Trial Registration:**

Current Controlled Trials: ISRCTN97185214.

## Background

Suicidal behaviour is a serious outcome of psychiatric illness in general, and is specifically associated with depression. It has been shown that the population attributable ratio (PAR) for depression in suicidal behaviour is 80 per cent (i.e. 80% of suicidal behaviour would be removed if depression did not occur [1]), and one in seven patients admitted to hospital for major depression will go on to die by suicide. Suicide ideation is one of the most consistently recurring symptoms of depression [2] and combined with the high risk of recurrence of depression (rising to 90% in people with 3 or more previous episodes), makes treatment of patients who have experienced suicidal depression extremely important.

Treatments designed to target suicidal behaviour have had mixed results [3]. Preventing recurrence of suicidal depression is likely to depend on being able to target the factors that underlie continuing vulnerability. Depression is one such vulnerability factor as most suicidal behaviour occurs in the context of depressed mood. However, it would also be useful to target specific vulnerability factors for suicidality directly.

Mindfulness Based Cognitive Therapy (MBCT, [4]) is a manualised treatment programme which has been shown to prevent relapse to depression in those who have experienced three or more depressive episodes in the past [5,6]), and is now recommended by the UK government National Institute for Health and Clinical Excellence as a treatment for prevention of depression recurrence in those with three or more previous episodes. However no studies to date have explored whether MBCT is effective in preventing relapse to depression when compared with a control psychological treatment of equal plausibility. Further the use of MBCT for the most severe recurrent depression - those people who become suicidal when depressed - has not been considered separately in previous published RCTs because participants have not been stratified according to history of suicidal ideation or behaviour.

Recently [name] and colleagues ([name], [name], [name] and [name]) adapted MBCT for use with patients suffering from recurrent suicidal depression (suicidal ideation or behaviour), to address this problem more directly. This treatment showed positive results in a pilot trial by significantly changing mood [7] and measures of ongoing psychological vulnerability from before treatment to after [8,9]. However, this previous trial did not include a follow-up, so we do not yet know if the change in vulnerability led to a reduction in relapse to depression and suicidality.

## Trial Objectives and Purpose

The objectives of this trial are to test whether Mindfulness-Based Cognitive Therapy (MBCT), a novel form of treatment combining mindfulness meditation and cognitive therapy for depression delivered in addition to treatment as usual (TAU), will reduce the risk of relapse to Major Depression in recurrently depressed patients and the incidence of suicidal symptoms in those with a history of suicidality who relapse. To this end we aim to compare MBCT with both TAU alone and Cognitive Psycho-Education (CPE), an equally plausible cognitive treatment, but without meditation.

Thus the study uses a "dismantling" paradigm in the sense that it removes meditation - the component of MBCT, the main treatment under investigation, that we hypothesize to be effective - to form CPE, the comparison treatment, which is otherwise identical in its content. Removal of the meditation component of MBCT from CPE allows us to assess, for the first time, the added benefits of the meditation component of MBCT in preventing relapse in people with a history of recurrent depression.

The study is also investigating potential mediators and moderators of treatment outcome by assessing symptoms, stressful life events, and aspects of cognitive functioning related to risk of relapse to depression - before and after treatment and during the follow-up period.

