Recurrence of suicidal ideation, both within episodes of major depression and over the follow-up period, is an important secondary outcome. Initially we shall examine recurrence of suicidality specifically for those participants who relapse to Major Depression and had a history of suicidal ideation or behaviour at entry to the trial. Then we shall compare severity of suicidal symptoms, as measured by the Beck Scale for Suicide Ideation (BSS current) and the MINI suicide-tracking measure, across the follow-up period for all participants, whether or not they relapsed or became suicidal. Finally we shall compare suicidal cognitions (and ability to let go of cognitions that occur), at baseline, T1 and T5 only between groups using AnCova, with T0 as covariate and T1 and T5 as separate outcomes.

By assessing cognitive measures relevant to risk of relapse to depression, namely mindfulness, suppression, self-compassion, rumination, self guides, autobiographical memory and executive capacity, before and immediately after treatment and at the end of follow-up, we can use them in an explanatory analysis to study factors that mediate efficacy. We shall use regression analysis (binary logistic regression for the dichotomous outcome of relapse and linear regression for the worst HRSD score during follow-up) to explore whether the change from T0 to T1 in each of these measures can account for the effects of treatment on risk of relapse.

Where necessary we shall transform variables closer to Normal distributions for AnCova. Where data are missing, we shall use data from alternative sources, notably therapists on the trial and referring general practitioners. We shall also use sensitivity analysis to assess the effect of including participants whose data on relapse is collected by these means.

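### The mediation models test each cognitive measure without change in depressive symptoms, so they cannot separate a specific cognitive mechanism from general mood improvement

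*Protocol article*

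**What the plan says.** - **Objectives.** The section Trial Objectives and Purpose says: "The study is also investigating potential mediators and moderators of treatment outcome by assessing symptoms, stressful life events, and aspects of cognitive functioning". Assessment is before treatment, after treatment and during follow-up.
- **Mediators analysed.** Appendix 1 lists the measures: "namely mindfulness, suppression, self-compassion, rumination, self guides, autobiographical memory and executive capacity". They are used "to explore whether the change from T0 to T1 in each of these measures can account for the effects of treatment on risk of relapse", through "binary logistic regression for the dichotomous outcome of relapse and linear regression for the worst HRSD score during follow-up". The Analysis section agrees: "We shall use cognitive measures to explore the extent to which they mediate relapse and recurrence during treatment and follow up".
- **Symptoms in the explanatory analyses.** Appendix 1 names baseline HRSD and BDI-II scores as potential moderators. The covariate rule in the Analysis section admits the baseline value of the dependent variable, and other baseline measures if they contribute significantly. Neither section enters change in symptoms over treatment.
- **Data available.** According to Outcome Measures and Appendix 1, HRSD and BDI-II are recorded at baseline, at T1 and at every follow-up.
- **Pilot.** The Background reports that the adapted treatment succeeded in "significantly changing mood [7] and measures of ongoing psychological vulnerability from before treatment to after".

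**The concern.** Randomisation protects the effect of treatment on a mediator. It does not protect the relation between the mediator and relapse. Anything that changes during treatment, moves with the cognitive measure and predicts relapse will distort that relation. Depressive symptoms are the obvious candidate:

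- The pilot changed mood and the vulnerability measures over the same interval.
- The plan treats residual symptoms as important enough to test as a moderator.
- Five of the seven listed measures (mindfulness, suppression, self-compassion, rumination, self guides) are questionnaires, which can plausibly shift with current mood.
- The second mediation outcome, worst HRSD during follow-up, is itself a symptom score.

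At stake is what the trial can say about how MBCT works. The Discussion offers the trial as a way to learn about mechanisms and to identify the critical therapeutic factors. A model without the rival explanation cannot tell the two accounts apart.

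**Working it through.** The plan states no figure for this analysis, so there is nothing to reproduce. The check has a textual part and an illustrative calculation.

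**1. Text.** The objectives list three kinds of factor, and the mediation analysis takes up one. Symptoms appear elsewhere only at baseline. A moderator needs only the baseline value; a mediator also needs the value after treatment, which is collected.

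**2. Algebra.** Let T be treatment, S symptoms (SD 1 within arm) and C a cognitive measure with no effect of its own on relapse. S and C can be read as T1 levels or as T0–T1 changes.

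- S = −δT + e
- C = rS + √(1−r²)·u
- outcome depends on bS + cT

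On a linear scale, the path from T to C is −rδ and the path from C to outcome given T is rb. The indirect effect credited to C is therefore −r²δb. The true symptom-mediated effect is −δb, so the share wrongly credited to C is r²: 0.4² = 16%, 0.5² = 25%, 0.6² = 36%, 0.7² = 49%.

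**3. Simulation.** From the Sample Size section: 120 MBCT v 120 CPE, with relapse 39% v 57%. Assumed, not in the document: r from 0.4 to 0.7; b = 0.5 or 0.8 (log-odds of relapse per SD of symptoms); and a rule that both paths reach p<0.05. The Sample Size section gives 0.45 SD as a detectable MBCT–CPE difference at ICC 0.05. It is not an expected effect on T1 symptoms, so 0.2 SD was run as well. Ranges span b = 0.5 to 0.8.

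| r | Inert measure passes, δ = 0.45 | Inert measure passes, δ = 0.2 |
|---|---|---|
| 0.4 | 8–16% | 3–7% |
| 0.5 | 17–33% | 5–7% |
| 0.6 | 30–51% | 9–15% |
| 0.7 | 47–65% | 13–18% |

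With symptoms also in the model, the rate at δ = 0.45 is 1–3%. Repeat runs agree within simulation error.

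**4. Does baseline adjustment suffice?** A separate simulation (symptom improvement of 0.5 SD, log-odds −0.8 per SD, inert measure) counted only the path from measure to relapse, so its rates are not comparable with the table. That path was significant in 35%, 74% and 96% of trials at an association of 0.3, 0.5 and 0.7. Adding baseline symptoms gave 36%, 74% and 97%. Adding symptom change brought the rate to about 5%. The baseline covariate rule therefore does not solve the problem.

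**5. The reverse order.** Now let treatment shift the cognitive measure by 0.45 SD, the measure drive symptoms, and symptoms drive relapse, so that the measure is a true mediator. The model without symptoms detects it in 27–91% of trials, the joint model in only 4–7%. Losing significance in the joint model therefore does not show that a measure is not a mediator.

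**The case against.** Several points on the other side have force.

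- **A reader might infer that the objectives promise symptoms as a mediator and that Appendix 1 breaks the promise.** The text does not support this. The objectives list mediators and moderators jointly and assign no role to each item. Appendix 1 does use symptoms, as baseline moderators. The sections are compatible, and the confounding problem does not need a broken promise.
- **A reader might infer that the trial will often declare false mediators.** The plan calls the analysis explanatory and sets no significance rule for mediation. The both-paths rule, r and b are assumptions. Two of the seven measures, autobiographical memory and executive capacity, are assessed by performance tasks, so correlations of 0.4–0.7 with mood should not be assumed for all seven.
- **A reader might want mediation claimed only if it survives adjustment for symptoms.** That rule would be unsound. The Interventions section describes maladaptive thinking as perpetuating low mood, which puts mood downstream of cognition. Step 5 shows that the rule would then miss nearly every true mediator acting through mood.
- **T1 symptoms can be part of the outcome.** Relapse is assessed from T1, and the T1 SCID covers the treatment phase. For someone who relapses during treatment, the T1 score may reflect the relapse itself. This stands and needs handling.
- **An article condenses.** Appendix 1 does not expressly exclude symptoms from the models. But it is headed as the statistical analysis plan and names its mediators one by one, and the Analysis section also names only cognitive measures. The gap is in what is written, not merely in detail left elsewhere.

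**Conclusion.** The concern holds in a limited form. As written, the mediation analysis cannot distinguish a specific cognitive mechanism from general mood improvement, although the data to address this are collected. The direction of the bias is secure whenever symptom change is related to both the measure and relapse; with no such relation there is no bias. Its size is not secure: roughly 3–18% of trials for a 0.2 SD symptom effect and 8–65% for 0.45 SD, at r of 0.4–0.7 and under a both-paths p<0.05 rule that the plan does not contain. The primary comparison and the randomised MBCT v CPE test of the meditation component are untouched. The change should be made because it alters what the exploratory mechanism analysis can conclude.

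**What to change.** In Appendix 1:

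1. Add T0–T1 change in HRSD or BDI-II as a candidate mediator, naming the scale in advance.
2. For each cognitive measure, report two models side by side: the measure alone, and the measure jointly with symptom change.
3. State the interpretation in advance. An effect that remains in the joint model is mediation beyond mood change. An effect that disappears is not distinguishable from mood change and is not evidence against mediation, because mood may lie on the path from cognition to relapse.
4. Add a sensitivity analysis excluding participants who relapsed before T1.

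The cost is wording and a few extra model fits on data already collected, with no new visits or measures. The price in reporting is a more cautious statement about mechanism.
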